### Data collection and management

Data are collected by trained research nurses/coordinators at each participating centre onto carbon copy paper Case Report Forms. Data entry and management are coordinated from the Data Management and Analysis Centre (DMAC) at The University of Adelaide under the direction of the study statistician ([name]). There are regular blinded reviews of data quality and data checks using established protocols. Data discrepancy inquiries and responses are managed through a secure web-based management information system.

The Case Report Forms are stored in a locked office at each study site. Only research staff directly involved in the study will have access to the information. Electronic forms of data are stored on secure servers at DMAC. Data are released only to persons authorised to receive those data.

Original/copies of study documents will be retained at each study site or in archives. No paper records are retained by DMAC at study closeout, all are returned to the coordinating centre, the Women’s and Children’s Health Research Institute. Documents will be retained for at least 30 years after study completion in line with the data retention schedules for research involving minors. At the completion of this time documentation will be destroyed using confidential document disposal. The study electronic data will be stored indefinitely on DMACs secure servers with access only granted to authorised study personnel.

### Statistical methods

All participants will be analysed according to the group to which they were randomised (intention-to-treat principle). The incidence of BPD will be compared between groups using a log binomial regression model with a generalised estimating equation used to account for dependence due to multiple births. The difference between the groups will be expressed as a relative risk with a 95 % confidence interval. Adjustment will be made for randomisation strata (study centre, sex and gestational age less than 27 completed weeks and 27 to less than 29 completed weeks). Secondary analyses will use log-binomial regression models for binary outcomes and linear regression models for continuous outcomes, with generalised estimating equations used to account for dependence due to multiple births. Missing data will be multiply imputed under a missing at random assumption. Sensitivity analyses will also be performed using the original unimputed data.

In planned sub-group analyses of the primary and secondary outcomes we will examine the effect of DHA supplementation on boys and girls separately, and on infants with gestational age less than 27 completed weeks or 27 to less than 29 completed weeks separately. Effect modification by these two factors (sex and gestational age) will be assessed separately by including interaction effects in the statistical models. Separate estimates of treatment effect will be obtained for males and females and for infants born less than 27 completed weeks’ gestation and 27 to less than 29 weeks’ gestation, independent of whether the interaction effect is statistically significant, since this is a priori of interest.

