#### Secondary outcome measures

A range of standard clinical outcomes for preterm infants < 29 weeks’ gestation are being collected including:Death before 36 weeks’ PMA or BPD;Respiratory support requirements including the duration of respiratory support from birth to 36 weeks’ PMA and from birth to 40 weeks’ PMA or discharge home whichever occurred first; discontinuation of endotracheal ventilation, non-invasive positive pressure support and low flow or supplemental oxygen to 40 weeks’ PMA or discharge home, whichever occurred first; the use of caffeine and total days caffeine from birth to 40 weeks’ PMA or discharge home, whichever occurred first; the use of postnatal steroids for lung disease ; the use of diuretics for lung disease and total days of diuretic use from birth to 40 weeks’ PMA or discharge home, whichever occurred first; the severity of BPD classified as mild/moderate/severe according to consensus definitions [1]; BPD classified according to supplemental oxygen or any respiratory support at 36 weeks’ PMA or discharge home whichever occurs first, according to clinical management at that time.Feeding tolerance assessed by number of days to reach enteral intake ≥ 120 mLs/kg/d and number of days on which one or more feeds were withheld up to the primary outcome.Growth – weight, length and head circumference z scores at 36 weeks’ PMA and 40 weeks’ PMA or discharge home, whichever occurred first.Deaths before 36 weeks' PMA and during 1^st^ hospitalisation.Length of hospital stay to first discharge home.Retinopathy of prematurity (stage ≥3), and that requiring treatment.Intra-ventricular haemorrhage – any grade and grade III or IV.Cerebral cyst formation – including periventricular leukomalacia and porencephalic cysts.Sepsis and necrotising enterocolitis.

Clinical data will be collected in accordance with the definitions of the Australia and New Zealand Neonatal Network [28].

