### Participant timeline

Infants will receive treatment from enrolment until 36 weeks’ PMA and follow-up will occur until 40 weeks’ PMA or to discharge home, whichever occurs first. At baseline, a 30 μL infant blood sample for fatty acid analysis will be taken, weight, length and head circumference will be measured and baseline clinical and demographic data collected. Weekly compliance data and monthly weight, length and head circumference measurements will be collected. At 36 weeks’ PMA the primary outcome will be assessed, infant weight, length and head circumference will be measured, an infant blood sample (30 μL) will be collected for fatty acid analysis and, if available, a 30 μL breast milk sample (also for fatty acid analysis) will be collected. Secondary outcome data will be collected up to 40 weeks’ PMA or discharge home, whichever occurs first. The date of first discharge home will also be recorded.

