### Sample size estimation

The rate of BPD in infants born less than 29 weeks’ gestation in the DINO trial was 51.4 %. To detect a 10 % absolute reduction (19 % relative reduction) in the incidence of BPD at 36 weeks’ PMA from 51.4 to 41.4 % (with 90 % power, two tailed α =0.05) between the DHA emulsion and control emulsion, a sample size of 1244 is required (622 per group). This sample size takes into account the clustering (non-independence) of multiple births (variance inflation factor 11 %) and deaths (4 % as estimated from the DINO trial). The variance inflation factor for multiple births was based on 26 % of infants born less than 29 weeks’ gestational age being from multiple births, an intracluster correlation coefficient for BPD of 0.52 and an average cluster size of 2.07 for these infants (as observed in the DINO trial in which mothers were randomised). While the variance inflation factor may be reduced by randomising infants rather than mothers, the calculated sample size ensures sufficient power even in the unlikely event that all infants from multiple births are randomised to the same treatment arm as their siblings.

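### The protocol names only the randomisation strata as adjustment; prespecifying baseline weight, length and head circumference as covariates would make the growth comparisons more precise at no cost

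*Protocol article*

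**What the plan says.** Growth is one of the key secondary objectives (Objectives). Under Secondary outcome measures the outcomes are "weight, length and head circumference z scores at 36" weeks' PMA, and again at 40 weeks' PMA or discharge home. The Participant timeline says that at baseline "weight, length and head circumference will be measured and baseline clinical and demographic data collected", so each growth outcome has a baseline counterpart.

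Under Statistical methods the text on secondary outcomes reads: "Secondary analyses will use log-binomial regression models for binary outcomes and linear regression models for continuous outcomes", with GEE for dependence between siblings. The one statement on adjustment names study centre, sex and gestational-age band. It comes after the description of the primary analysis and before the sentence on secondary analyses. No baseline measurement is named as a covariate for any outcome, and none is excluded. The same section commits to separate treatment estimates by sex and by gestational-age band for primary and secondary outcomes, whether or not the interaction is significant.

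**The concern.** An infant's size at baseline can be expected to predict its size some weeks later. Where that holds, a model without baseline size leaves explainable variation in the residual, and the treatment comparison has a wider confidence interval than it needs. The named strata may be only a partial substitute. Sex and gestational age are factors for which growth z scores are normally already standardised, although centre may still explain some variation.

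What is at stake is the precision of a key secondary outcome, most of all in the subgroup estimates, where numbers are smaller. The covariate is also best chosen before unblinding, because a choice made afterwards invites doubt about selective reporting.

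**Working it through.** **The plan's own figure.** The document gives no power, SD or correlation for growth. Its sample size concerns BPD: "incidence of BPD at 36 weeks’ PMA from 51.4 to 41.4" %, "with 90 % power, two tailed α =0.05", leading to "a sample size of 1244 is required (622 per group"), after allowing for "clustering (non-independence) of multiple births (variance inflation factor 11 %) and deaths (4 % as estimated from the DINO trial").
- Two-proportion formula, 51.4 % against 41.4 %, two-sided 0.05, 90 % power: 521 per group, or 541 with continuity correction.
- With continuity correction: 541 × 1.11 / 0.96 = 625.5, so 626 per group and 1252 in total, 0.6 % above 1244.
- Without continuity correction, inflation 1.11: 603 per group, 1206 in total.
- Without continuity correction, inflation rebuilt from the stated inputs as 1 + 0.26 × (2.07 − 1) × 0.52 = 1.145: 622 per group, exactly 1244.

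The total is therefore reproducible to within 1 % and can be used for growth.

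**Effective size for growth.** 622 × 0.96 / 1.11 = 538 per group. This assumes that the BPD-based inflation factor also applies to growth, with or without the baseline covariate. With 1.145 it would be 522, and the unadjusted detectable difference below would move from 0.198 to 0.201 SD.

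**Effect of the baseline covariate.** Let r be the partial correlation between baseline and outcome z score given the strata. Under randomisation:
- variance with baseline / variance without = 1 − r², so the share of attainable precision given up by omitting it is r²;
- narrowing of the confidence interval = 1 − √(1 − r²);
- difference detectable with 90 % power, in SD units = (1.960 + 1.282) × √(2/538) × √(1 − r²).

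The document gives no r, so the range is an assumption.

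| r | Variance cut (r²) | CI narrower by | Detectable difference, 90 % power | Power for 0.2 SD |
|---|---|---|---|---|
| 0 (no baseline) | – | – | 0.198 SD | 91 % |
| 0.2 | 4 % | 2 % | 0.194 SD | 92 % |
| 0.5 | 25 % | 13 % | 0.171 SD | 97 % |
| 0.7 | 49 % | 29 % | 0.141 SD | above 99 % |
| 0.8 | 64 % | 40 % | 0.119 SD | above 99 % |

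**Subgroups.** The split by sex or gestational-age band is not given. If it is assumed to be equal, each subgroup has 538 / 2 = 269 effective infants per group, and √(2/269) = 0.0862.
- No baseline: 3.242 × 0.0862 = 0.28 SD detectable with 90 % power; power for 0.2 SD about 64 %.
- r = 0.5: 0.28 × 0.866 = 0.24 SD; about 76 %.
- r = 0.7: 0.28 × 0.714 = 0.20 SD; about 90 %.

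**The case against.** The strongest objection is that the text is silent rather than wrong. A reader might infer that the growth z scores will be analysed without baseline size. The document does not say so: it gives one model family for all continuous secondary outcomes and no closed covariate list for growth. Outcome-specific covariates are commonly left to the analysis plan, which is not shown. This stands, and the point is therefore a suggestion and not a demonstrated fault. It does not dispose of the point, because the section does name an adjustment set, and someone following it would fit the strata at most.

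A reader might also conclude that a quarter to a half of the attainable precision is being lost. That range is simply r² for an assumed r of about 0.5 to 0.7. The documents do not support it, and over r = 0.2 to 0.8 the loss runs from 4 % to 64 %. Baseline is taken around the start of enteral feeding, and the dosing rule under Administration allows for a period before birthweight is regained, so baseline weight could be a noisy predictor. The correlation could also differ between the 36-week and the later assessment.

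Nor is there bias. Randomisation protects the unadjusted estimate, and its confidence interval already reflects chance imbalance in baseline size. With the full sample, power for a 0.2 SD difference is about 91 % even without the covariate. That is a fair limit on the importance of the point, but it applies less to the subgroup estimates.

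Finally, the strata sentence is not expressly limited to the primary outcome. Saying that it extends to secondary outcomes would be a clarification only.

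**Conclusion.** The point holds as a minor, cost-free improvement. Growth is a key secondary outcome, the matching baseline measurements are collected, and the only adjustment named is for the strata. Whenever r exceeds zero, following the text as written gives less precise growth comparisons than the data allow. The variance reduction on offer is 4 % to 64 % for r between 0.2 and 0.8, and the confidence interval would narrow by about 2 % to 40 %. These figures rest on assumed correlations. The detectable differences also assume the BPD-based inflation factor and, for the subgroups, an equal split.

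The documents do not support reading this as an error in the plan, as a source of bias or as a threat to the primary analysis. No stated figure changes.

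**What to change.** Add one sentence to the analysis text, or confirm that the analysis plan already contains it: in the linear GEE model for each growth z score (weight, length, head circumference; at 36 weeks' PMA and at 40 weeks' PMA or discharge), the corresponding baseline z score is a covariate alongside the randomisation strata, and the same model is used for the subgroup estimates. It would help to state in the same place whether strata adjustment applies to all secondary outcomes. This should be settled before unblinding. It needs no new data, no change in sample size and no change to trial conduct.

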### Data monitoring and harms

An independent Trial Monitoring Committee has been set up to review the progress of the trial and provide feedback to the Trial Management Committee. The Trial Monitoring Committee reviews general study progress (recruitment, compliance, loss to follow-up), the BPD event rate and key secondary/safety outcomes. The Trial Monitoring Committee provides advice regarding external issues that may impact on the N3RO trial (for example changes in clinical practice). The committee meets annually or as required and consists of two neonatologists with clinical trials experience, and a statistician with clinical trials expertise.

An independent (blinded) Serious Adverse Event Committee has been established to review serious adverse events. There are no serious adverse events which would be anticipated as a unique consequence of participation in the trial, however all deaths are to be reported. The Serious Adverse Event Committee includes experts in neonatology and pathology who are not involved in the trial. The primary role of the Serious Adverse Event Committee is to review all deaths to determine whether there is any likelihood that involvement in the trial could have contributed to the death. The cause of the death is determined from the autopsy results or other hospital summary of the death by the relevant medical personnel. This committee meets six monthly, or as required.

Any event that in the opinion of an Investigator may be of immediate or potential concern for an infant’s health or well-being is to be reported immediately to the Chair of the Steering Committee. Expected events such as necrotising enterocolitis, BPD, intracranial abnormality, pulmonary haemorrhage and patent ductus arteriosus are captured by data collection in the Case Report Form. These data are available for review by the Trial Monitoring Committee.

### Research ethics approval

This protocol and the informed consent document have been approved by the Human Research Ethics Committee (HREC) of each study site. Australia: Southern Adelaide Clinical HREC (Coordinating HREC and Flinders Medical Centre, Adelaide); Women’s and Children’s Health Network HREC (Women’s and Children’s Hospital, Adelaide); The Royal Women’s Hospital HREC (Royal Women’s Hospital, Melbourne); The Southern Health HREC (Monash Medical Centre); Mercy Health HREC (Mercy Hospital for Women, Melbourne); Women and Newborn Health HREC (King Edward Memorial Hospital, Perth); Hunter New England HREC (John Hunter Hospital, Newcastle; Liverpool Hospital, Sydney; Royal Hospital for Women, Sydney; Mater Mothers’ Hospital, Brisbane). New Zealand: Northern B Health and Disability HREC (Wellington Hospital, Wellington; Waikato Hospital, Hamilton). Singapore: SingHealth Centralised Institutional Review Board E (KK Women’s and Children’s Hospital).

Any subsequent modifications will be reviewed and approved by the HREC of each study site. The study will be conducted in compliance with the current version of the protocol. Any change to the protocol document or informed consent form that affects the scientific intent, study design, patient safety, or may affect a participant’s willingness to continue participation in the study will be considered a major amendment. All such amendments will be submitted to the HREC for approval. Any other changes to the protocol (such as administrative changes to dates and study personnel) will be considered minor amendments and will be notified to the HREC as appropriate.

## Discussion

This protocol describes a randomised controlled trial comparing the effect of an enteral emulsion providing supplementary DHA (60 mg/kg/day) with a control enteral emulsion containing no DHA on the incidence of BPD in preterm infants born < 29 weeks’ gestation. BPD is a serious complication of preterm birth, associated with long-term morbidity. Both animal and human studies point to the possibility that DHA may have a primary role in the prevention of BPD however there have been no randomised controlled trials designed specifically to determine the effect of DHA on BPD. To the best of our knowledge this is the first such randomised controlled trial. Results from this study will provide the first high quality evidence on whether an enteral DHA supplement reduces the incidence of BPD in very preterm infants.

## Abbreviations

AA, arachidonic acid; BPD, bronchopulmonary dysplasia; DHA, docosahexaenoic acid; DINO, the acronym is derived from ‘**D**ocosahexaenoic Acid (DHA) for the **i**mprovement of **n**eurodevelopmental **O**utcomes’ in Preterm Infants; DMAC, data management and analysis centre; EPA, eicosapentaenoic acid; GMP, code of good manufacturing practice; HREC, Human Research Ethics Committee; LA, linoleic acid; LCPUFA, long-chain polyunsaturated fatty acid; N3RO, the acronym is derived from ‘**N-3** fatty acids for improvement in **R**espiratory **O**utcomes’; NHMRC, National Health and Medical Research Council of Australia; PMA, postmenstrual age
